### Participants and setting

Participants will be recruited through residential aged-care facilities. Residential aged-care facilities within Australia are government-funded organisations that provide additional support for families who may have a family member with dementia, whereby many move from their residential homes into a residential aged-care facility so that they can be monitored and provided with additional care. PASS^2019^ power analysis and sample size software (ncss.com/software/pass; NCSS, Kaysville, UT, USA) was used to derive the sample size. The Neuropsychiatric Inventory Questionnaire–Nursing Homes (NPI-NH) is the primary outcome measure. Total sample size for a 2 × 2 crossover design assuming a two-sided *t* test to detect a mean difference of 6 on the NPI-NH scale with a standard deviation of 13 (for the difference) is 40 for a power of 80% and significance level of 5%. Fifty participants will be recruited to allow for a 20% attrition rate. Participants will be eligible to participate if they live in a residential aged-care facility, are aged 65 years or older, have a diagnosis of mild dementia (indicated by a score ≥ 20 on the Mini Mental State Examination [MMSE]), are able to speak English, are known as compliant with taking medication, are not bedridden, and are able to provide informed consent. Participants will be excluded if they have certain health conditions, such as frontotemporal or Lewy body dementia; have other comorbidities, such as epilepsy, anorexia nervosa, comorbid psychiatric conditions, Parkinson’s disease, or congestive heart failure; have a history of myocardial infarction or anginal pain, stroke, liver disease, or renal disease; or are taking medications such as primidone, phenobarbital, carbamazepine, rifampicin, rifabutin, troglitazone, *Hypericum perforatum*, and valproic acid that may interact with cannabis metabolism.

The pre-/post-surveys and focus group discussions are an exploratory, qualitative component of this study, and thus a definitive sample size calculation cannot be determined at this stage. We estimate that six focus groups comprising six to eight participants, including two groups of residential care staff, activity staff (care staff who monitor daily activities and social engagement), and family members, will ensure that data saturation has been reached. Written informed consent will be obtained from all participants, including the residential aged-care staff and the next of kin.

### Rigor

Residential aged-care staff usually work within the aged-care setting for at least 3 months and therefore are likely to be working in the same facility for the duration of the 4-month trial. The same aged-care staff member will monitor the same participant(s) for the duration of the study and report any changes on the participants’ behalf. To be classified as a residential care staff member, the individual must spend at least two occasions per week with the participant. The same registered nurse will administer the medication for both treatment cycles.

### Recruitment

The residential aged-care clinical and general managers who have established relationships with the participants and their next of kin will promote the study to those they feel would be eligible to participate. This will be performed through face-to-face conversations.

### Randomisation

The randomisation process for this study will be done by creating a random number list using a 1:1 ratio allocation to ensure an equal number of cases in both the placebo group (*n* = 25) and the treatment group (*n* = 25) using Excel software (Microsoft Corp., Redmond, WA, USA). The determination of participant allocation will be completed by the laboratory manager in the drug manufacturing laboratory, with each case being provided a unique identification (ID) number (1–50). The primary researcher, who is responsible for recruitment, will provide the laboratory manager with the participant’s name to be sequentially matched against with the next available ID number. The laboratory will provide the pharmacy with both CBM and placebo in identical bottles labelled with the ID, but the medical practitioner and research team members will not know the order of treatment until the completion of the study. The pharmacist will place the participant’s name on the bottle before distributing the bottles to the aged-care facilities.

### Blinding

This is a double-blind study. Therefore, the laboratory manager will be the only individual who will know the group allocation for the participants. This is to ensure that the pharmacist, aged-care staff, medical practitioners, research nurse, family members/next of kin, participants and researchers are all blinded to the participant’s group allocation. Once the study is complete, the laboratory manger will un-blind the information by providing the primary researcher with a list of participants and their group allocation in order to conduct the analysis.

### Procedure

The study will run for 18 weeks, comprising a 2-week eligibility period for screening and clinical assessment and a 16-week experimental phase encompassing two 6-week cycles of treatment and placebo separated by a 2-week washout period between the treatment cycles and a 2-week washout period following the completion of the second arm (Fig. 1).

**Fig. 1 Fig1:**
[figure not shown]
The key phases of the 18-week trial

#### Eligibility period

Individuals who express interest in participating in the study will initially be screened on the basis of inclusion criteria (described above). Following the initial screening process, potential participants will undergo a thorough clinical investigation by a geriatrician to ensure they have the cognitive capacity to provide informed consent using the MMSE. The MMSE [45] is the most widely used cognitive outcome measure to assess the severity of cognitive performance. It comprises 11 items, where a total score out of 30 can be calculated to assess the severity of dementia (25–30 = questionably significant, 20–25 = mild, 10–20 = moderate, 0–10 = severe). Those who seem suitable will be revisited by the geriatrician 1 week after the cognitive tests and will confirm that the participant has understood the purpose of the trial and has recalled the details of the study. Then the primary researcher will invite the eligible participants to enrol in the study and ask them to complete the consent form and provide some demographic and baseline information, including age, sex, education level, weight, medical history including comorbid illnesses, and prescribed medications. The participants will then be randomly allocated to treatment group A or B and receive either CBM oil or placebo for the first 6-week treatment cycle. No adjustments will be made to the participants’ currently prescribed medications.

#### Experimental phase

This phase of the study will take 16 weeks to complete. To minimise the risk of adverse events and variation in the maximum tolerated dose of CBM oil, each participant will receive one dose on the first and second days (2 pm) and two doses (9 am and 2 pm) for the reminder of both treatment cycles. A registered nurse will administer the dose along with a small meal (e.g., morning and afternoon tea), and the rate of titration will be monitored by the pharmacist to ensure it is appropriate for each individual. The participant will gradually receive an increased dose (titration) of the medication over several weeks, as shown in Table 1. During these weeks, the participant along with the care staff will record the presence of, and any change in, any potential adverse events that may be associated with the medication after the first dose, each afternoon when the dose is increased, and again on the final day of medication. If an adverse event is noted, the participant will revert to their previous best tolerated dose using the adverse events and safety protocol listed below.

**Table 1 Tab1:** Titration administration, including dose and number of sprays

Day(s)	Week	Dose administered (daily)		Number of spray(s) per dose	Adverse events recorded (time)
		9 am	2 pm		
**1**, 2	1	–	**2.5 m**g	1	3 pm
**3**, 4	1	2.5	2.5	1	
**5**, 6	1	2.5	**5**	1–2	3 pm
**7**, 8	1	5	5	2	
**9**, 10	2	5	**10**	2–4	3 pm
**11**, 12	2	10	10	4	
**13**, 14	2	10	**15**	4–6	3 pm
**15**, 16	2/3	15	15	6	
**17**, 18	3	15	**20**	6–8	3 pm
**19**, 20	3	20	20	8	
**21**, 22	3/4	20	**25**	8–10	3 pm
**23**, 24	4	25	25	10	3 pm

Adverse events will be recorded 1 h after drug administration on days of dose increase (days bolded) and on the last day of the treatment period

An upper limit of 50 mg/day of THC will be permitted in those who do not experience any adverse events from the medication. Once a participant has reached their maximum tolerated dose (or a total of 50 mg/daily of THC), they will continue to receive that dose until the cessation of the 6-week period. The placebo group will follow a similar titration process using the indicated volumes shown in Table 1. They will continue to receive an increase in the volume of medication until they record an onset of an adverse event, at which time they will continue to take that volume of placebo until the end of the 6-week placebo cycle.

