### Aims

The primary aim of the present study will be to see if a purified CBM oil is safe and improves behavioural and neuropsychiatric symptoms of dementia (BPSD). In addition, two secondary aims of this study will include examining QOL and discomfort caused by pain among patients with dementia receiving CBM oil.

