### Data analysis

#### Quantitative

The results of questionnaires completed on behalf of the aged-care staff, participants and family members will be analysed using IBM SPSS Statistics version 25 software (IBM, Armonk, NY, USA). The responses from the aged-care staff will be the main responses considered for analysis. Where available, participants and family responses will be included for secondary analysis. To examine group differences, the participants will be categorised according to their treatment cycle group allocation (group A or group B). Descriptive statistics will be derived. Each variable will be tested for normality. For those variables that meet the normality assumption, two-sided paired and/or independent *t* tests will be used to examine group differences within and between groups. If the normality assumption is violated, then non-parametric tests such as the Wilcoxon signed-rank test will be used. Within-subject differences of the four measurements between the first and second washout periods will be tested using paired *t* tests to ensure that the washout phase is long enough to rule out any carryover effects [51, 52]. All data collection points will be examined using general linear mixed modelling techniques to see if any changes in behaviour, QOL or pain have occurred over the duration of both treatment cycles. The covariates of weight, average dose of medication, and baseline measures will be controlled for in each model, and any interactions will be tested and reported. The proportion of adverse events during the CBM and placebo phases will be tested and reported for each individual. NPI-NH is the primary outcome measure for this study. All other measures (CMAI, QOL-AD, and Abbey Pain Scale) have been included for secondary analysis. The CMAI will be analysed using the reliability change methodology compared with the NPI-NH to allow small changes to be reported [53]. The α-value will be set at 0.05. In the instance where a participant withdraws halfway through a treatment cycle, the information collected prior to withdrawal will be retained in the study because their personal information will have been de-identified. The data management of the information collected will follow standard university procedures, be stored in a locked cabinet for a period of 15 years, be stored on a password-protected computer, and be backed up regularly in a secure format.

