## Appendix

### Adverse events associated with THC and CBD

Adverse events will most likely occur within 1 h of administration of the medication but will often resolve within 48 h of treatment. Participants will report their adverse events to make sure the titration is appropriate for them.

Compared with how you normally feel, have you experienced a change in any of the symptoms described below in the last hour? Tick the most appropriate box below.

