**Table Taba:**

	No	Yes (tick box below)				
		Better	Somewhat better	Same as usual	Somewhat worse	Much worse
Drowsiness/fatigue						
Dizziness						
Dry mouth						
Sore throat						
Anxiety						
Nausea						
Memory decline or attention deficits						
Joy or euphoria						
Blurred vision						
Headache						
Paranoia						
Depression						
Lack of coordination						
Diarrhoea						
Appetite						
Sleep disturbance						

To be completed during the titration phase and following the last dose in each treatment arm

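### The adverse event recording rules disagree, no form is scheduled on days 25 to 41, and no group-level CBM versus placebo comparison is stated for the safety part of the primary aim

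*Protocol article*

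**What the plan says.** The Aims section gives safety first place: "The primary aim of the present study will be to see if a purified CBM oil is safe and improves behavioural and neuropsychiatric symptoms". The Data analysis section names one primary measure, an efficacy scale: "NPI-NH is the primary outcome measure for this study".

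Recording of adverse events is described in four places:

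- **Table 1 footnote (Experimental phase):** "Adverse events will be recorded 1 h after drug administration on days of dose increase (days bolded) and on the last day".
- **Table 1 column for the recording time:** 3 pm on the rows starting at days 1, 5, 9, 13, 17, 21 and 23, and empty on the rows starting at days 3, 7, 11, 15 and 19. All twelve starting days are bolded.
- **Body text above the table:** recording takes place "after the first dose, each afternoon when the dose is increased, and again on the final day of medication".
- **Adverse events and safety protocol:** participants report one hour after the raised dose. These reports feed the decision on whether the dose goes up again.

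The form is in the Appendix. It asks "have you experienced a change in any of the symptoms described below in the last hour", and its note on use reads "To be completed during the titration phase and following the last dose in each treatment arm".

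The only analysis given for these data, under Data analysis (Quantitative), is: "The proportion of adverse events during the CBM and placebo phases will be tested and reported for each individual".

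**The concern.** If the footnote, the column and the text give different recording days, sites can follow the protocol in good faith and still collect different data. The same records steer titration, so the inconsistency affects conduct as well as reporting.

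Two further features bear on what the trial can say about safety. First, use of the form is confined to titration and the end of each cycle, so the stretch at the final dose has no structured adverse event record. An analysis plan written later cannot recover events that nobody recorded. Second, forms follow dose increases, so the number of forms per person can differ between participants and between a person's two cycles. A proportion of adverse events then has no common denominator. An analysis reported person by person would not by itself estimate the effect of CBM on adverse events, which is what the safety part of the aim needs.

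**Working it through.** **1. Recording days under each rule.** The inputs are the 9 am and 2 pm doses in Table 1. Each row's daily total is compared with the row before.

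| Row starts on day | 9 am / 2 pm (mg THC) | Daily total (mg) | Which dose rises | Time in column |
|---|---|---|---|---|
| 1 | – / 2.5 | 2.5 | 2 pm | 3 pm |
| 3 | 2.5 / 2.5 | 5 | 9 am | blank |
| 5 | 2.5 / 5 | 7.5 | 2 pm | 3 pm |
| 7 | 5 / 5 | 10 | 9 am | blank |
| 9 | 5 / 10 | 15 | 2 pm | 3 pm |
| 11 | 10 / 10 | 20 | 9 am | blank |
| 13 | 10 / 15 | 25 | 2 pm | 3 pm |
| 15 | 15 / 15 | 30 | 9 am | blank |
| 17 | 15 / 20 | 35 | 2 pm | 3 pm |
| 19 | 20 / 20 | 40 | 9 am | blank |
| 21 | 20 / 25 | 45 | 2 pm | 3 pm |
| 23 | 25 / 25 | 50 | 9 am | 3 pm |

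The total rises on all 12 bolded days, 6 times through the 2 pm dose and 6 times through the 9 am dose. Recording days per 42-day cycle are:

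- Footnote: 12 + last day = 13 (13/42 = 31%).
- Column: 7 + last day = 8 (8/42 = 19%).
- Body text, if it means days when the afternoon dose rises: 6 + last day = 7 (7/42 = 17%).

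The last reading explains all five blanks, but it would leave day 23 blank too. No single rule fits all three sources.

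**2. One-hour timing.** Every time in the column is 3 pm, one hour after the 2 pm dose. One hour after a 9 am dose would be 10 am, which does not appear. On day 23 the form falls six hours after the raised dose and asks about 2 pm to 3 pm. So 0 of 6 morning increases have a tabulated assessment one hour later, although the safety protocol asks for one after the increased dose.

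**3. Time at the final dose.** Titration in Table 1 ends on day 24 and the cycle ends on day 42, when the last form is due. Days 25 to 41 are 41 − 25 + 1 = 17 days, and 17/42 = 40%. This applies to a participant titrated without delay. The gap is longer for someone who settles at an earlier step and may be shorter for someone whose increases are postponed.

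**4. What nurse visits could add.** At the twice-weekly frequency in the safety protocol, 17 days contain about 2 × 17/7 = 4.9, or roughly 5, visits. At the weekly frequency for heart rate and blood pressure in the Abstract it would be 2 or 3. The two sections differ and should be aligned.

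**5. Sample size.** The stated size concerns NPI-NH only. ((1.960 + 0.842) × 13/6)² = 36.8. The noncentral t gives 81.2% power at n = 40 with 38 degrees of freedom, and 40/0.8 = 50. The plan's figures reproduce and are untouched by this point, but they were not set for safety.

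**6. What a paired comparison could show.** The article gives no event rates, so these are assumptions. Let a be the proportion with an event under CBM only and b the proportion with an event under placebo only. Power of the exact McNemar test (two-sided 0.05) is:

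| a / b | Risk difference | 40 pairs | 50 pairs |
|---|---|---|---|
| 0.20 / 0.05 | 0.15 | 36% | 48% |
| 0.30 / 0.10 | 0.20 | 44% | 55% |
| 0.30 / 0.05 | 0.25 | 74% | 85% |
| 0.40 / 0.10 | 0.30 | 74% | 84% |

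Only large differences would be detected reliably. The interval estimate should therefore lead, and a non-significant result would not show safety.

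**The case against.** **Other monitoring exists.** A reader might infer that safety rests on the one-hour form alone. The article does not support that. The safety protocol adds nurse visits with heart rate and blood pressure, regular weight and body composition, staff vigilance early in titration and a nurse review two days into each washout. This stands as a limit on the point. It does not close the gap, because at those visits the nurse is to discuss existing adverse event records, and no new form is scheduled between the end of titration and the last dose.

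**The blanks have a logic.** On each blank day the morning dose rises to a level already taken, and recorded, at 2 pm two days before. The Appendix also expects most events within an hour of dosing, so a short window has a rationale. This stands for five of the six morning increases. It does not reconcile the footnote or day 23. If the blanks were only merged cells in the printed table, the times would still all be 3 pm and step 2 would be unchanged.

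**Bias toward a finding of safety.** A reader might infer that events are under-counted where the drug causes them, because forms stop when titration stops. The documents do not establish this. Postponed increases are attempted again and bring further forms. A participant halted for a moderate or severe event already counts in an endpoint of at least one such event. The text on placebo holds the volume once an adverse event is recorded and mentions no second attempt, which could reduce recording under placebo instead. The number of forms can differ; the direction of any bias is not known.

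**The analysis sentence is compressed.** A reader might infer as many as 50 separate significance tests. The sentence can also mean that proportions under CBM and placebo are tested, and also reported per person. It names no test, and a fuller analysis plan may exist. What stands is that the wording is ambiguous and states no group-level comparison.

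**Conclusion.** The point holds as a contradiction within the Experimental phase section, together with one badly fixed analysis sentence. Three sources give 13, 8 and (on the narrow reading of the text) 7 recording days per cycle. Five of 12 dose-increase days have no time in the table, and none of the six morning increases is tabulated for assessment at one hour. No form is scheduled on 17 of 42 days for a participant titrated to day 24.

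This rests on three assumptions: that the table's empty cells are truly empty, that titration runs without delay, and that no fuller document schedules more forms. The counts are firm on that basis. The effect on the safety result cannot be sized or signed from the article. The matter should be corrected because it touches the first-named part of the primary aim and the remedy is cheap. It does not affect the NPI-NH sample size.

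**What to change.** 1. **Reconcile the recording rules.** Bring the Table 1 column, its footnote, the body text and the safety protocol to one rule that says on which days and at what time the form is due, including on days when only the 9 am dose rises. Which titration rule applies is for the clinical team, but the sections must agree.
2. **Make recording independent of dose steps.** Complete the form on the same fixed days in both cycles, whether or not the dose rose, and at the already planned research-nurse visits to day 42. At those visits, ask about the time since the last record, with care-staff input. Settle the visit frequency first. The cost is a few minutes per visit, a little more form-filling and some recall error in people with memory loss, which staff input should reduce.
3. **State a group-level analysis.** Compare, within participants, the occurrence of at least one 'Somewhat worse' or 'Much worse' event under CBM and under placebo. Use McNemar's test, or conditional logistic regression with period, and give the risk difference with a 95% CI. Keep individual listings as description only. This costs a few sentences of analysis text. Given the power in step 6, the interval should be read as an estimate and not as proof of safety.

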### Adverse events and safety protocol

An adverse events protocol will be put into place to minimise any potential harm or risks of receiving additional medication [14]. This will include participants reporting if they have experienced any adverse events 1 h after the increased dose has been administered (*see* Appendix). If moderate to severe adverse events are recorded (determined as ‘Somewhat worse’ (moderate) or ‘Much worse’ (severe) on the participant’s adverse event record) and these events have not ameliorated by the time for the next dose, the participant will receive the previous best tolerated dose. If the effects of the adverse event(s) have disappeared or become milder and do not interfere with the participant’s daily functioning or well-being, the registered nurse may increase the dose at the indicated rate. Recurrence of adverse events after two attempts to increase the dose will result in the participants remaining at their previous best tolerated dose for the remainder of the intervention period. A participant who experiences an adverse event will stay on the previous dose for another 2 days before the next dose is increased. At the beginning of the titration phase, a staff member at the aged-care facility will be vigilant in monitoring any acute adverse events such as dizziness, discoordination with a danger of falls and injury, and extreme fatigue. Any adverse events recorded will be reported to a facility line manager and will then be communicated to staff during shift changes.

Additional safety monitoring will be completed by a research nurse who will meet with each participant to discuss their adverse event records and measure their heart rate and blood pressure twice per week. In addition, the participant’s weight and non-invasive body composition measures such as lean body mass, bone mass, body fat percentage, and fat mass will be measured once per week using a portable scale. In addition, a nurse-led review will be completed 2 days into the washout periods to monitor the participant’s withdrawal symptoms once no more medication is being administered.

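### The placebo-only dosing rule after an adverse event contradicts the rule for all participants, and blinded staff cannot apply it

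*Protocol article*

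**What the plan says.** The protocol article gives two instructions for what happens after an adverse event during titration.

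- **All participants.** Experimental phase first says "If an adverse event is noted, the participant will revert to their previous best tolerated dose" and refers the reader to the safety protocol. Adverse events and safety protocol gives the detail without distinguishing arms. If a moderate or severe event is recorded and "these events have not ameliorated by the time for the next dose, the participant will receive the previous best tolerated dose". If the event has gone or become milder, the nurse may increase again. "A participant who experiences an adverse event will stay on the previous dose for another 2 days before the next dose is increased". The dose is fixed only later: "Recurrence of adverse events after two attempts to increase the dose will result in the participants remaining at their previous best tolerated dose" for the rest of the period.
- **Placebo.** The last sentence of Experimental phase has placebo recipients go on increasing, within the 6-week cycle, "until they record an onset of an adverse event, at which time they will continue to take that volume of placebo until the end".

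On who could act on an arm-specific rule, Randomisation says "The laboratory will provide the pharmacy with both CBM and placebo in identical bottles labelled with the ID", and Blinding says "the laboratory manager will be the only individual who will know the group allocation for the participants". A registered nurse gives the doses and "the rate of titration will be monitored by the pharmacist". Blinding lists the pharmacist and the aged-care staff among those who do not know the allocation.

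**The concern.** The placebo sentence tells staff to stay at the volume at which the event occurred. The general rule tells them to go down a step. A frail resident with an event at a new step therefore has two written instructions. The placebo instruction also depends on knowledge that no one at the bedside or in the pharmacy has. Safety is part of the primary aim (Aims), so the rule that governs dose after an event should be single and usable under blinding. What is at stake is the dose that residents take after an event, should anyone follow the wrong sentence.

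**Working it through.** **1. The two rules side by side**

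| | All participants | Placebo sentence |
|---|---|---|
| Trigger | moderate or severe event that persists to the next dose | any onset |
| Action | go back one step | stay at the event volume |
| Re-escalation | after a 2-day hold; fixed only after recurrence on two attempts | none |

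Describing the placebo titration as similar does not reconcile them, because the sentence that follows spells out a different action.

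**2. Can the placebo sentence be applied by arm?** No. The bottles look the same and carry only an ID (the pharmacist adds the participant's name), and neither the nurse nor the pharmacist knows the allocation. The sentence can only be ignored or applied to every bottle.

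**3. Size if it were applied to every bottle**

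Inputs: Table 1 gives, for steps starting on days 1, 3, ..., 23, daily sprays of 1, 2, 3, 4, 6, 8, 10, 12, 14, 16, 18, 20. The top step is kept from day 25 to day 42. One spray of active oil is 2.5 mg THC (Management and administration of medication). With no event the cycle total is 588 sprays, or 588/42 = 14.0 sprays/day.

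First events are placed at the 3 pm recording points in Table 1. Day 1 is left out because no lower step exists. Three cycle totals are compared:

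- *Freeze*: the event volume is kept to day 42.
- *Two failures*: 2 days at the lower step, a 1-day re-attempt that fails, 2 more days, a second 1-day failure, then the lower step to day 42.
- *One hold*: 2 days at the lower step, then 2-day steps, all tolerated.

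Worked example, first event on day 13. Days 1 to 12 total 2 × (1+2+3+4+6+8) = 48 sprays.

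- Freeze: 48 + 30 × 10 = 348 sprays; 348/42 = 8.29 per day.
- Two failures: 48 + 10 + 16 + 10 + 16 + 10 + 23 × 8 = 294; 294/42 = 7.00 per day.
- One hold: 48 + 10 + 16 + 20 + 24 + 28 + 32 + 36 + 17 × 20 = 554; 554/42 = 13.19 per day.

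Freeze minus two failures = 54 sprays × 2.5 = 135 mg THC more. Freeze minus one hold = −206 sprays × 2.5 = 515 mg less, or about 12 mg/day less (515/42).

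| First event, day | Freeze (sprays) | Two failures | One hold | Freeze − two failures (mg THC) | Freeze − one hold (mg THC) |
|---|---|---|---|---|---|
| 5 | 120 | 85 | 535 | +87.5 | −1037.5 |
| 9 | 224 | 162 | 542 | +155 | −795 |
| 13 | 348 | 294 | 554 | +135 | −515 |
| 17 | 456 | 410 | 566 | +115 | −275 |
| 21 | 548 | 510 | 578 | +95 | −75 |
| 23 | 588 | 554 | 584 | +85 | +10 |

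**4. Sensitivity**

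- If no re-attempt is made, the excess is the daily step difference times the days left. That runs from 2.5 × 37 = 92.5 mg (day 5) to 5 × 33 = 165 mg (day 9).
- If the two attempts include the first increase, so that one re-attempt is made, one day's difference comes off: 90 to 160 mg.
- Counting events on every bolded day from day 3 lowers the bottom of the two-failure range only to 2.5 × 35 − 2 × 2.5 = 82.5 mg (day 7).

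**The case against.** The strongest defence is that the sentence is loose wording. Just before it, Experimental phase says that anyone who reaches the maximum tolerated dose stays on it to the end of the 6 weeks. The placebo sentence has the same shape and may be meant as the placebo counterpart of that plateau. Experimental phase also points by name to the safety protocol, so staff who cannot tell the bottles apart would most likely follow that and come to no harm. This stands as an argument about likely consequences. It does not remove the contradiction: staying at the event volume is the opposite of stepping back, and nothing in the article says which text prevails.

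A reader might infer three stronger conclusions. The documents do not support them.

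- *The sentence unblinds the trial.* It would have to be used by arm first, and the identical bottles and restricted allocation list prevent that.
- *It builds an arm difference into the average-dose covariate named in Data analysis.* This also needs by-arm use, and it assumes that placebo dose is counted in sprays, which the article does not say. In mg of THC the placebo dose is zero under either rule. In volume, arms could differ under the safety protocol too, if active oil causes more events.
- *Residents on active oil will be overdosed.* Staff would have to apply a sentence expressly about placebo to every bottle. Even then, exposure could be lower rather than higher.

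**Conclusion.** The point holds as a contradiction in a stated dosing rule. The placebo sentence conflicts with the rule for all participants in trigger, action and re-escalation, and it cannot be carried out in a double-blind trial with identical bottles. It should be corrected before first dosing.

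The harm is conditional and can go either way. If the sentence were applied to every bottle, a resident on active oil would receive about 85 to 155 mg more THC over the cycle than under the safety protocol when two re-attempts fail. When one hold is enough and later steps are tolerated, the resident would receive 75 to 1037.5 mg less for first events from day 5 to day 21, and 10 mg more for an event on day 23.

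These figures assume that the first event falls at a 3 pm recording point, that each failed re-attempt lasts one day, and that each later step lasts 2 days. The article gives no event rates, so neither the frequency nor the net direction can be stated. The planned sample size does not depend on this point.

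**What to change.** Delete the last sentence of Experimental phase. In its place, state that the rule in Adverse events and safety protocol applies identically, expressed in spray volumes, to both bottles and both treatment cycles. The same wording should go into the site dosing instructions.

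The cost is one deleted sentence and one added before first dosing. It needs no extra participants, visits or staff.
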